## Abstract

**Background:**

An emerging field of research describes the role of *pre*operative health behaviours, known as prehabilitation. The preoperative period may be a more physically and emotionally salient time to introduce and foster chronic adherence to health behaviours, such as exercise, in patients compared to post-treatment during recovery. Moreover, physical and psychosocial improvements during the preoperative period may translate into an enhanced recovery trajectory with reduced operative complications and postoperative adverse effects. No studies have assessed prehabilitation for men with prostate cancer undergoing radical prostatectomy.

**Methods/Design:**

This is a multi-centre, pilot randomized control trial conducted at two Canadian urban teaching hospitals. 100 men undergoing radical prostatectomy for prostate cancer with no contraindications to exercise will be recruited and randomized to the prehabiliation program or usual care. Prehabilitation participants will engage in a preoperative, individualized exercise program including pelvic floor muscle strengthening instructions and a healthy lifestyle guide for men with prostate cancer. These participants will be asked to engage in 60 minutes of home-based, unsupervised, moderate-intensity exercise on 3–4 days per week. Usual care participants will receive the same pelvic floor muscle strengthening instructions and healthy lifestyle guide only. We will assess the feasibility of conducting an adequately powered trial of the same design via recruitment rate, programmatic adherence/contamination, attrition, and safety. Estimates of intervention efficacy will be captured through measurements at baseline (4–8 weeks preoperatively), within 1 week prior to surgery, and postoperatively at 4, 12, and 26 weeks. Efficacy outcomes include: fatigue, quality of life, urinary incontinence, physical fitness, body composition, aerobic fitness, pain, and physical activity volume.

**Discussion:**

The primary outcome of this study is to determine the feasibility of conducting a full-scale, randomized controlled trial of prehabilitation versus usual care and to estimate effect sizes that will inform sample size determinations for subsequent trials in this field. To our knowledge, this is the first study to examine a structured presurgical exercise program for men undergoing radical prostatectomy for prostate cancer. This trial will advance our understanding of strategies to efficiently and effectively use the preoperative period to optimize postoperative recovery.

**Trial registration:**

Clinicaltrials.gov Identifier: NCT02036684

## Background

Radical prostatectomy (RP) is the most common and effective treatment for localized prostate cancer (PCa), with a 15-year survival rate of approximately 90% [1, 2]. Unfortunately, RP is associated with significant adverse effects, such as urinary incontinence, sexual dysfunction, and reduced physical function that collectively diminish health-related quality of life (HRQOL); such decrements may persist for up to two years postoperatively [3, 4]. Given the efficacy of RP and its widespread use in the management of PCa, it is suggested that the metric of surgical success should include more than simply disease-free survival; rather, it should include a comprehensive assessment of physical and psychosocial wellbeing and the rate at which the patient returns to baseline levels of wellbeing [1, 5].

Traditionally, interventions intended to improve RP recovery and minimize adverse effects were limited to the postoperative period. Such approaches have typically focused on the urological side effects of urinary incontinence and sexual dysfunction through pelvic floor muscle exercises (PFMX) and/or phosphodiesterase-5 inhibitors while psychotherapy is commonly employed for psychological adjustments in the postoperative period [5–8]. Overall, research suggests that patients are often non-adherent to the prescribed postoperative interventions [9]. Furthermore, little attention has been directed towards the general physical and functional declines that RP patients experience, despite their significant contribution to overall HRQOL [10, 11]. Strassels et al. [12] found that physical functioning one month post-RP was below population norms and that 43% were dissatisfied with their physical ability. At 3 months post-RP, Litwin et al. [13] found that only 30% and 36% of patients had returned to baseline values of physical function and energy levels, respectively. Given that the recovery from RP may be blunted by postoperative decreases in physical functioning and concomitant non-compliance with traditional post-RP treatments, examination of interventions applied in the pre-surgical phase is warranted.

To enhance the overall surgical experience for patients, an important question revolves around *when* the most opportune time is to introduce recovery-optimizing behaviours. The postoperative period may be less than ideal due to concerns related to perturbing the healing process as patients await additional results or treatments. Instead, an emerging field of research describes the role of preoperative strategies to improve treatment tolerance and recovery. The preoperative period may be more physically and emotionally salient for patients by capitalizing on: i) the generally better physical condition of the patient (compared to the acute postoperative period), ii) surgical wait-list times, and iii) a ‘teachable moment’ for the patient that accompanies the need for major surgery [14]. Ultimately, it appears that the preoperative period may be an optimal time to invest into the modifiable factors that contribute to peri- and postoperative health.

A health behaviour that has demonstrated great promise in terms of its beneficial relationship with perioperative complications and postoperative recovery is physical activity and the consequential improved physical fitness levels. Studies routinely report that patients who are physically active and fit recover more quickly, have fewer perioperative complications, and experience better convalescence compared with patients who are less physically active and fit [15–21]. *Pre*-habilitation is defined as the process of enhancing one’s functional and mental capacity to enable him/her to withstand a significant stressor [22]. In a surgical setting, preoperative physical and/or psychological conditioning aims to increase body and mind reserves to prevent the declines in postoperative wellbeing [22]. Recently published systematic reviews of prehabilitation have described numerous benefits to postoperative wellbeing across a variety of surgical populations [23–25], including cancer-patients specifically [26]. Carli and colleagues have shown that prehabilitation can improve postoperative physical function in cancer patients undergoing colorectal surgery [27, 28], hysterectomy [29], and lung resection [30]. Their group has also found that improvements in physical function were associated with improvements in mental health, vitality, and self-perceived health [31]. Moreover, it appears that control subjects whose fitness deteriorated preoperatively had more surgical complications and greater need for intensive care [31].

With respect to PCa patients undergoing RP, we have previously shown in an observational study that physical activity in the year prior to RP is associated with improved postoperative HRQOL [32]. Additionally, in a cohort of 509 patients undergoing RP, we observed that men who were meeting physical activity guidelines prior to surgery had greater HRQOL at 6 and 26 weeks postoperatively compared to men who were not meeting the PA guidelines [33]. Moreover, we found that men who were active preoperatively were less likely to report being incontinent 6 weeks after surgery than their inactive counterparts. Exercises targeted at the pelvic floor have also shown benefit for RP patients as two studies have demonstrated effectiveness at improving urinary incontinence by 20% compared to controls [34, 35]. These studies have revealed an important role for physical activity and fitness in the postoperative wellbeing of men undergoing RP; however, no randomized controlled trial has been conducted to determine a causal relationship between preoperative exercise and postoperative outcomes in this population. Thus, there remains an important opportunity to examine a comprehensive prehabilitation program for men undergoing RP for PCa that may have a profound influence on surgical preparation by reducing the often-chronic nature of complete recovery from this procedure.

## Methods/Design

This study is a 2-arm, multi-centre, pilot randomized controlled trial to examine the effect of a comprehensive prehabilitation program (PREHAB) versus usual care (UC). The primary objective of this study is to assess the feasibility of conducting of an adequately powered study of similar design. Our secondary objective is to report estimates of efficacy on several clinically important outcomes for RP patients.

This study will be conducted at two urban Canadian teaching hospitals: the Princess Margaret Cancer Centre in Toronto, Ontario, and the McGill University Health Centre in Montreal, Quebec. Both participating institutions have received approval from their respective research ethics boards.

### Study recruitment and randomization

Eligible patients will be recruited from ambulatory urology clinics at each site by a research coordinator (RC). Recruitment posters will also be placed in hospital waiting areas. Written informed consent will be collected from all patients prior to participation.

Participants will be randomly allocated to either the PREHAB or UC groups prior to the baseline assessment, stratified by study site. Blinded allocation of participants to their treatment groups will be performed via sequentially numbered opaque envelopes that will contain intervention assignments that have been shuffled to create a random order. Figure 1 provides the structure of participant flow through each intervention arm.

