**Participant flow.**

### Study arms

Both groups will begin participation in their respective study arms at the time of randomization following shortly after RP scheduling. The duration of the preoperative wait-time (typically 4-8 weeks) will be recorded. Both groups will receive a copy of a PCa-specific lifestyle support book containing information on topics such as nutrition, active-living, and pelvic floor training [38].

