#### PREHAB

PREHAB participants will engage in an individualized, total-body exercise and PFMX program. The total-body exercise prescription will consist of 60 minutes of home-based, unsupervised exercise on 3–4 days per week. Each session will be individualized, based upon a baseline assessment and will include: a 5-minute warm-up, 25 minutes of aerobic exercise (40-60% of heart rate reserve; HRR), 25 minutes of resistance training (5 exercises targeting major muscle groups performed at an intensity of 8–12 repetitions maximum), and a 5-minute cool-down. Training intensity progression will occur when the participant can complete aerobic exercise with mild exertion and/or when the participant can complete 15 repetitions of a given resistance exercise. Participants will be provided with varying intensities of resistance bands, a stability ball, and an exercise mat. The PFMX prescription will begin with instructions on how to engage the pelvic floor delivered by the RC trained in PFMX. The PFMX prescription will include a gradual increase in repetitions from 60 per day during weeks 1–2, 120 per day during weeks 3–4, and 180 per day during week 5 to the surgical date. The total number of repetitions of the PFMX will be divided equally between the rhythmic contractions (contract and relax over one second) and the sustained contractions (contract and hold for up to 10 seconds). Participants will be instructed to contract with maximal effort during all PFMX repetitions. The PREHAB intervention will be supported with a manual (translated into French) and exercise videos created by the co-investigating team. The RC will communicate with the PREHAB participants weekly via phone or email to ensure program compliance, support appropriate progression, and address any barriers to exercise that may prevent ongoing participation.

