### Outcome assessments

Self-report measures and physical fitness assessments will be conducted at: baseline (following RP booking, prior to beginning group assignment) approximately 4–8 weeks preoperatively, within 1 week prior to RP, and at 4, 12, and 26 weeks postoperatively. All self-reported measures are available in English and French.

Full-scale trial feasibility will be assessed by: 1) recruitment rate (and reasons for non-participation); 2) attrition rate; and 3) adherence and contamination (through a physical activity log completed by the RC during the weekly communication). Adherence to the exercise prescription for the PREHAB intervention and to the PFMX prescription for both groups will be analyzed by calculating the percentage of total physical activity volume prescribed (i.e. total number of repetitions completed/total number of repetitions prescribed).

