### Statistical analysis

Participant characteristics will be summarized using descriptive statistics (mean, standard deviation, frequency). The equivalence of groups at baseline in terms of demographic and clinical variables will be assessed using independent samples t-tests for continuous variables and chi-square tests for categorical variables. We will report recruitment and attrition rates per site with comparison between sites using the chi-square test. Adherence to the PREHAB and PFMX prescriptions will be compared across study sites using independent samples t-tests. Estimates of efficacy (Group and Time main effect, as well as Group x Time interactions) will be analyzed using a repeated-measure analysis of covariance (ANCOVA), controlling for the baseline value of the outcome of interest and study site. Frequency of perioperative complications will be compared between the PREHAB and UC groups using chi-square analysis and as per the Clavien-Dindo classification system [58]. Length of stay between the PREHAB and UC groups will be compared using independent samples t-test.

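### The stated order of randomisation, baseline assessment and start of the arms does not hold together, and randomising first exposes the self-reported and effort-dependent ANCOVA covariates to knowledge of the arm

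*Protocol article*

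**What the plan says.** Four parts of the protocol article bear on the order of events.

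- Study recruitment and randomization: "Participants will be randomly allocated to either the PREHAB or UC groups prior to the baseline assessment, stratified by study site". Allocation uses concealed envelopes: "Blinded allocation of participants to their treatment groups will be performed via sequentially numbered opaque envelopes".
- Study arms: "Both groups will begin participation in their respective study arms at the time of randomization following shortly after RP scheduling".
- Outcome assessments: baseline is described as "baseline (following RP booking, prior to beginning group assignment", about 4 to 8 weeks before surgery. Questionnaires and fitness tests are both taken then.
- PREHAB: "Each session will be individualized, based upon a baseline assessment".

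The Statistical analysis section then estimates efficacy with a repeated-measures ANCOVA, "controlling for the baseline value of the outcome of interest and study site". Length of stay is compared by t-test and complications by chi-square, with no baseline covariate.

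**The concern.** Baseline adjustment is safe when the covariate cannot have been influenced by the assigned arm. The randomisation section gives the one order under which that is not guaranteed. The intervention is an exercise programme that a man cannot fail to recognise. The article describes concealment of the sequence, which protects enrolment, but no masking of participants or assessors when baseline is measured.

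Many of the measures respond to expectation or effort: FACT-P, FACT-F, HADS, PDI and CHAMPS are self-reported, and the 6MWT, grip strength and elbow dynamometry depend on effort. A man who already knows his arm may answer or perform differently, and the model would treat that difference as if it had existed before treatment.

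Two further things are at stake. A man who leaves between allocation and baseline has no covariate value and would drop out of a complete-case ANCOVA, possibly more often in one arm. And attrition and recruitment are both feasibility outcomes, so the order decides which of them such a man counts towards.

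**Working it through.** **1. Do the statements fit together?**

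- (a) Randomisation comes before baseline (Study recruitment and randomization).
- (b) The arms start at randomisation (Study arms).
- (c) Baseline comes before group assignment begins (Outcome assessments).

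If (c) means before allocation, it contradicts (a) directly. If (c) means before the assigned programme starts, it fits (a) alone, giving the sequence allocate, baseline, start. But (b) leaves no interval between allocation and start, so baseline cannot fall between them. On either reading, (a), (b) and (c) are not all literally true. The PREHAB section adds to the strain on (b): exercise individualised from a baseline assessment cannot start at randomisation if baseline is still to come.

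**2. What a distorted covariate does.** The article gives no effect size, standard deviation or correlation, so there is no stated figure to reproduce. The inputs below are assumptions, in SD units:

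- rho, the baseline-to-follow-up correlation: 0.5 to 0.7
- d, the shift in one arm's measured baseline caused by knowing the arm: 0.1 to 0.3
- f, the shift in the same arm's follow-up measure from the same cause

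Bias in the adjusted group effect = f - rho x d.

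**3. Baseline distorted, follow-up not (f = 0).** This was simulated with no true effect, a single follow-up, a two-sided 5% test and 20,000 trials per setting. Group sizes were 50 per arm, and 40 per arm after the anticipated 20% attrition (50 x 0.8 = 40).

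| rho | d | bias = -rho x d | rejection rate, 40 per arm | rejection rate, 50 per arm |
|---|---|---|---|---|
| 0.5 | 0.1 | -0.05 | 5.9% | 5.9% |
| 0.5 | 0.2 | -0.10 | 8.0% | 8.6% |
| 0.5 | 0.3 | -0.15 | 11.4% | 13.3% |
| 0.7 | 0.1 | -0.07 | 7.2% | 7.5% |
| 0.7 | 0.2 | -0.14 | 13.7% | 16.4% |
| 0.7 | 0.3 | -0.21 | 25.2% | 29.7% |

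The simulated mean bias matched the formula to within 0.001 SD. With d = 0 the bias was 0.00 and the rejection rate 5.0 to 5.1%. The bias does not shrink as the sample grows.

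**4. Follow-up distorted as well.** A man who knows his arm at baseline also knows it at every later assessment. With d = 0.2 and f = 0.2:

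- rho = 0.5: 0.2 - 0.5 x 0.2 = +0.10 SD
- rho = 0.7: 0.2 - 0.7 x 0.2 = +0.06 SD

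The net bias is zero when f = rho x d, that is f = 0.10 for rho = 0.5 and f = 0.14 for rho = 0.7. The sign therefore depends on quantities that the article does not give.

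**5. Which outcomes are reached?** Those that are baseline-adjusted and self-reported or effort-dependent. Length of stay and complications have no covariate. The accelerometer is worn only after surgery, so it has no baseline value. BMI, waist circumference and impedance body fat have a baseline, but a mechanism that works through reporting or effort hardly reaches them.

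**The case against.** The strongest reply is that this is loose wording. The phrase in Outcome assessments can be read as before starting the assigned programme, and the Study arms sentence may give approximate timing only. A reader might infer that one section plainly puts randomisation after baseline. It does not: that phrase is ambiguous, and the conflict appears only when the three sections are read together and literally. The participant-flow figure is not available here; it might show the intended order, but it would not make the sentences agree. Nor does this reply help with the design point, because the order in the randomisation section is explicit.

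Second, being allocated is not the same as being told. The article does not say when the man or the coordinator learns the arm, and the full protocol might describe masking at baseline. This stands: knowledge of the arm at baseline is an inference, so the harm is conditional.

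Third, a reader might infer that baseline could be measured after exercise has begun. The PREHAB section argues against that, since the sessions are built from the baseline assessment.

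Fourth, one could take the table as showing that the treatment effect will be understated by a definite amount, or that every efficacy result is compromised. Neither is supported. The table assumes that follow-up is undistorted, and with equal distortion the sign reverses. In that case the baseline shift even offsets part of the follow-up shift (+0.06 to +0.10 SD against +0.20 SD with a clean baseline). Such an offset would be accidental and could not be verified, so it is no reason to keep the order.

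Finally, unequal loss before baseline is a possibility and not something the article shows. Such withdrawals could be counted, provided the order is fixed.

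**Conclusion.** The point holds in a limited form. The three statements on order cannot all be literally true, and the explicit one, randomising before baseline, leaves self-reported and effort-dependent covariates open to influence by the assigned arm. The baseline-adjusted estimates for those outcomes can be biased. With d = 0.2 SD, rho of 0.5 to 0.7 and f between 0 and 0.2 SD, the net bias lies between -0.14 and +0.10 SD. All of these inputs are assumed, so the range illustrates the mechanism and does not estimate its size or direction in this trial. The conclusion also assumes that the arm is known by the time baseline is measured, which the article neither states nor excludes.

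This should be fixed, but it does not undermine the trial. The primary objective is feasibility, and the baseline covariate plays no part in recruitment, adherence or contamination. It still matters because the article intends the effect sizes to inform sample sizes for later trials, and because the order settles how men lost before baseline are classified.

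**What to change.** - Study recruitment and randomization: state that the next envelope is opened only after written consent and completion of the whole baseline assessment.
- Study arms: state that both arms start after that point.
- Outcome assessments: replace the ambiguous phrase with a plain statement that baseline is completed before randomisation.

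Men who leave before the envelope is opened then count as non-participants, and men who leave afterwards count as attrition with a baseline value in hand. The change removes distortion of the covariate. It does not remove any effect of knowing the arm on follow-up responses, which remains in an open trial.

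The cost is a wording change and a reordering of existing steps, with no added participants or assessments. The article does not say whether randomisation and baseline share a visit; if they do not, there may be a small scheduling burden. If randomisation must come first for practical reasons, the article should say how baseline is protected, for example by an assessor unaware of the arm and by telling the man his assignment only after the assessment.

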**Figure 1 Fig1:**
[figure not shown]
**Participant flow.**

### Study arms

Both groups will begin participation in their respective study arms at the time of randomization following shortly after RP scheduling. The duration of the preoperative wait-time (typically 4-8 weeks) will be recorded. Both groups will receive a copy of a PCa-specific lifestyle support book containing information on topics such as nutrition, active-living, and pelvic floor training [38].

